### Primary study outcome

#### Intracranial progression-free survival

The primary study outcome is iPFS, defined as the number of months from the start of TOMO or conventional 3D-CRT/IMRT to the occurrence of the first evidence of disease progression, which will be evaluated according to the Response Evaluation Criteria in Solid Tumors.

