**Methods:**

This is a randomized, controlled, prospective study including 102 SCLC patients with brain metastases randomized (1:1) to the experimental (whole brain radiation therapy for synchronous brain metastases with irradiation to protect the hippocampus) or control (whole brain radiotherapy for sequential brain metastases to boost irradiation) group. The sample size is calculated through a single-sided test; 102 participants will be required for the main results to have statistical and clinical significance. We aim to provide clinical trial data support for better prognostic treatment options in patients with SCLC and brain metastases. The clinical trial data include both the primary and secondary outcomes; the primary outcome is the intracranial progression-free survival time after the new technology application. The secondary study outcomes include the assessment of neurological function, the quality of life, and the overall survival rate. Follow-up consultations will be conducted every 2 months. After the final patient completes follow-up, the Statistical Product and Service Solutions software will be used for scientific and rigorous data analysis. Version 1.0 of the protocol was implemented on January 1, 2021; the recruitment process for this clinical trial commenced on April 1, 2021, and will end on March 31, 2024.

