Currently, TOMO is often used for a variety of diseases [22–24]; however, the clinical value of TOMO in the treatment of SCLC brain metastasis remains controversial. There is a substantial difference regarding the dose distributions of the abovementioned technologies. Based on theoretical and model studies, it has been long speculated that different doses may result in different prognostic outcomes. Therefore, this study sought to use TOMO technology to implement WBRT synchronous irradiation of brain metastases with increased radiation doses, while protecting the key functional areas of the hippocampus.

Our primary hypothesis is that TOMO will increase the clinical intracranial progression-free survival (iPFS) time by approximately 5–8%, owing to the higher accuracy of the treatment plan regarding location and dose of local tumor control. Our secondary hypothesis is that neurological function will be better protected due to the accuracy of this therapy. In the future, we hope to develop intervention methods and improve the corresponding treatment protocols based on the results of this clinical trial. This clinical trial is expected to further improve the efficacy of radiotherapy and improve the quality of life and survival of patients.

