#### Post TOMO follow-up

After radiotherapy, patients will be reviewed every 2 months for a total of 6 months to evaluate whether they have recurrence and to determine their neurological function status. During 6 months to 2 years after treatment, a re-check will be performed every 6 months. The examination will include a brain MRI test, routine blood tests, and liver and kidney function tests, which will be used to evaluate the effectiveness of the therapy according to the standards set by the committee. The follow-up period for iPFS and OS is 2 years. In addition, we will assess the neurological function and QoL immediately post radiotherapy and at 1 month, 3 months, 6 months, 1 year, and 2 years post RT. The research outline is shown in Fig. 2 and Table 2.

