### Roles and responsibilities

The study sponsor and funders provide financial support in the research, and they will not have ultimate authority over any of these activities. The coordination center, steering committee, endpoint decision committee, and data management team are composed of all authors. Each item is a monthly regular meeting to monitor its quality. The coordination center is responsible for coordinating all resources, the steering committee guides the smooth progress of clinical trials, the endpoint adjudication committee is in charge of the ruling of endpoint events, and the data management team is responsible for monitoring the authenticity and quality of the data.

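### The definition of the primary endpoint, iPFS, neither restricts progression to the brain nor counts death, so it does not match the endpoint's name

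*Protocol article*

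**What the plan says.** The abstract of the protocol article states that "the primary outcome is the intracranial progression-free survival time after the new technology application". The only definition is under Primary study outcome, where iPFS is "defined as the number of months from the start of TOMO or conventional 3D-CRT/IMRT" up to "the occurrence of the first evidence of disease progression, which will be evaluated according to the Response Evaluation Criteria in Solid Tumors". The sentence does not say where in the body progression must occur, and it does not mention death.

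Three other places bear on the reading:

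- **Background.** The primary hypothesis expects longer iPFS "owing to the higher accuracy of the treatment plan regarding location and dose of local tumor control".
- **Post TOMO follow-up.** Reviews take place every 2 months up to 6 months and then every 6 months up to 2 years. "The examination will include a brain MRI test, routine blood tests, and liver and kidney function tests". No imaging outside the brain is listed. "The follow-up period for iPFS and OS is 2 years".
- **Data analysis.** iPFS and overall survival are both to be estimated by Kaplan-Meier. No event or censoring rule for iPFS is added there or in the study outline table. Death appears only in the overall survival definition.

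**The concern.** An endpoint with this name should answer how long a patient stays alive and free of progression in the brain. The written event departs from that in two ways.

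**Death is not an event.** A patient who dies with no documented progression never reaches the endpoint as defined. In a Kaplan-Meier analysis the usual consequence is censoring at death, which treats the patient as if still at risk of progressing later. The curve then describes time to progression. Such deaths could easily arise, because after month 6 the brain MRIs are 6 months apart and a patient can die between scans.

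**Site is not restricted.** Taken at its word, the definition lets progression outside the brain end iPFS. The hypothesis is about local tumour control from brain radiotherapy, so such events would add noise to the comparison. With no extracranial imaging scheduled, they would also come to light unsystematically.

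Two analysts following this text could count different events in the same patients, and the result would be the trial's primary result.

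**Working it through.** **1. Name against definition**

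| Element | Implied by name and hypothesis | Written definition |
|---|---|---|
| Site of progression | Brain | Not stated; disease progression by the solid-tumour criteria |
| Death | An event (progression-free *survival*) | Not mentioned |
| Imaging listed | Brain MRI | Brain MRI only |
| Time origin | – | Start of radiotherapy |

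The overall survival, follow-up and data analysis sections do not supply the two missing elements.

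**2. The plan's own figure**

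The sample size section gives 2 × [(1.96 + 0.842) × 1.8 / 1]² = 2 × 5.0436² = 50.9, rounded to 51 per arm. This reproduces. It is a two-means formula on months and uses neither events nor hazards. Changing the event definition therefore leaves the stated 102 unchanged, but the figure also says nothing about power under either definition.

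**3. Deaths censored or counted (illustration)**

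The document gives no event rates, so all inputs are assumptions: independent exponential times, a median of 8 months to intracranial progression, and a median of 12 months to death without it, also halved and doubled to show a range. Extracranial progression is left out here.

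- Deaths censored, at 12 months: 2^(−12/8) = 2^(−1.5) = 35.4%; median 8.0 months.
- Deaths counted, at 12 months: 2^(−12/8 − 12/12) = 2^(−2.5) = 17.7%; median 1/(1/8 + 1/12) = 4.8 months.

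| Assumed median to death | Deaths censored | Deaths counted |
|---|---|---|
| 6 months | 35.4% | 2^(−3.5) = 8.8% |
| 12 months | 35.4% | 2^(−2.5) = 17.7% |
| 24 months | 35.4% | 2^(−2.0) = 25.0% |

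**4. Extracranial progression counted (illustration)**

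Assume that treatment affects only intracranial progression, with hazard ratio h, and that other progression occurs in both arms at r times the control intracranial hazard. The hazard ratio for any progression is (h + r)/(1 + r). Two-sided power is Φ(½√d × |ln HR| − 1.96), with d = 102, that is, every patient having an event.

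| r | HR if h = 0.60 | Power | HR if h = 0.70 | Power |
|---|---|---|---|---|
| 0 | 0.60 | 73% | 0.70 | 44% |
| 0.5 | 0.73 | 35% | 0.80 | 20% |
| 1 | 0.80 | 20% | 0.85 | 13% |
| 2 | 0.87 | 11% | 0.90 | 8% |

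This shows direction only.

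**5. Dilution from adding death (illustration)**

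With medians of 8 and 12 months, a progression hazard ratio of 0.60 and equal death hazards in the arms, the composite hazard ratio is (0.60/8 + 1/12)/(1/8 + 1/12) = 0.1583/0.2083 = 0.76. With a median to death of 6 months it is (0.60/8 + 1/6)/(1/8 + 1/6) = 0.83, and with 24 months it is (0.60/8 + 1/24)/(1/8 + 1/24) = 0.70.

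**The case against.** The best defence is that the intent is clear. The endpoint is called intracranial, the hypothesis is about local control, and the only imaging listed is of the brain. A reader might infer from the definition that the trial has chosen to count progression anywhere in the body. The document does not support that: it fails to restrict the site, which is different from a rule that extracranial progression counts. This part stands as a correction to the site wording. It does not remove the point, because the definition is what an analyst must implement. It also does nothing for the omission of death, on which no context helps.

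It can also be said that censoring rules are commonly left to an analysis plan or full protocol. That is fair for detail, but which outcomes are events is the core of the definition, and the article states one that contradicts the name. It is also true that censoring of deaths is an inference. The data analysis section removes patients who do not complete examinations or follow-up from the efficacy analysis, so a death might lead to exclusion instead.

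The 35% against 18% could be read as evidence of a biased comparison. It is not. It describes one arm, rests on assumed medians, and shows a shift in level. Under the same independence assumption, censoring deaths does not bias the hazard ratio for progression. Nothing in the document indicates that mortality differs between the arms.

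Finally, a reader might infer biased event decisions from "The coordination center, steering committee, endpoint decision committee, and data management team are composed of all authors". The document says that participants are not blinded and is silent on whether those judging endpoints are masked. Unmasked adjudication is therefore not established and forms no part of this point. Nor does the time origin, since the document gives no ground here for changing it.

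**Conclusion.** The point holds in this form: the only definition of the primary endpoint does not match its name, because progression is not restricted to the brain and death is not an event. Followed literally, with deaths presumably censored, it yields time to any progression. This follows from reading the text and needs no assumption beyond the handling of deaths.

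The size is illustrative. With deaths censored instead of counted, the 12-month estimate would be about twice as high at the assumed medians (35% against 18%), and the gap depends strongly on the assumed death rate. If extracranial progression were in fact counted, the curve as written would lie below 35%, and the treatment effect would be diluted as in the hazard ratios of step 4. The definition has to be settled before the primary analysis, because otherwise it is unclear what the primary result estimates.

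**What to change.** Reword the primary outcome as follows:

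- **Event:** first intracranial progression on brain MRI, or death from any cause, whichever comes first.
- **Not an event:** extracranial progression alone.
- **Censoring:** patients without an event are censored at the last adequate brain MRI. Only observed deaths count; the overall survival section's habit of taking the last visit as the time of death for patients lost to follow-up should not carry over.
- **Secondary analysis:** cumulative incidence of intracranial progression with death without progression as a competing event.

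The time origin can stay as written. The brain MRIs and death dates are already to be collected, so no scans are added and the stated 102 does not change.

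The real cost is statistical. Deaths unrelated to intracranial control pull the composite towards no difference: from an assumed 0.60 to about 0.76, or 0.70 to 0.83 over the range of death rates above. The competing-risk analysis helps to show how much of the composite result comes from intracranial control, and the protocol should state this trade-off.

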### Secondary study outcomes

#### Assessment of neurological function

The Expanded Disability Status Scale (EDSS) assessment will be used to standardize the neurological examination, and each system will be scored according to the degree of dysfunction.

#### Quality of life

Quality of life (QoL) will be assessed using the European Organization for the Research and Treatment of Cancer Quality of Life Questionnaire (EORTC QLQ-C30) (version 3) in patients with brain metastases caused by SCLC at the baseline and every 2 months after treatment. The questionnaire is available as an attachment to the paper.

#### Overall survival

Overall survival (OS) refers to the number of months between the radiotherapy procedure and the time of death or last follow-up. For patients who are lost to follow-up prior to death, the time of the last follow-up visit is usually calculated as the time of death.

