### Data analysis

After the last patient completes the follow-up study, the committee will assess the occurrence of the primary and secondary endpoints. Treatments in participant timeline are all routine medical orders, and patients will follow the medical advice. If there is any failure to review on time, a phone call will be reminded. If the patient fails to complete the relevant examination, evaluation or follow-up within the agreed time, or cannot suspend the study, part of the clinical trial of the patient will be suspended. The data of these patients will be marked on the record and not entered in the final curative effect analysis system. The fixed staff is responsible for the input of data, coded into groups 1 and 2 according to their treatment plans, and set a password for the database to protect the privacy of patients’ data. Data quality is controlled by the Data Quality Supervision Committee.

Data will be organized and analyzed using the SPSS 25.0 software, and *P* < 0.05 will be considered significant in all statistical tests. iPFS and OS will be calculated using the Kaplan-Meier method. Assessment of neurological function will be scored using the EDSS assessment scale, and QoL will be scored using the FACT-G. The chi-squared test will be used in combination with propensity matching analysis to minimize differences due to smoking, sex, weight loss, geographic factors, economic status, and education level and to avoid baseline effects to the greatest extent possible. Definition of analysis population relating to protocol non-adherence is that the patients who do not follow. In addition, we use the multiple imputation method to handle missing data.

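### As written, overall survival gives patients lost to follow-up a death at their last visit, and the Data analysis section states two further, incompatible rules for the same patients

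*Protocol article*

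**What the plan says.** The Overall survival section of the protocol article measures OS as "the number of months between the radiotherapy procedure and the time of death or last follow-up". It then adds a rule: "For patients who are lost to follow-up prior to death", "the time of the last follow-up visit is usually calculated as the time of death".

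The Data analysis section names the estimator, "iPFS and OS will be calculated using the Kaplan-Meier method", without a censoring rule. The same section says of patients who do not complete an examination, evaluation or follow-up in the agreed time: "The data of these patients will be marked on the record and not entered in the final curative effect analysis system". It closes with a general statement that "we use the multiple imputation method to handle missing data", tied to no endpoint.

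Under Post TOMO follow-up, "The follow-up period for iPFS and OS is 2 years". Visits are two-monthly for the first six months, and after that, "During 6 months to 2 years after treatment, a re-check will be performed every 6 months".

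**The concern.** Kaplan-Meier handles a patient last known alive by censoring: the patient counts as at risk up to the last contact and then leaves the risk set without an event. The sentence in the Overall survival section gives that patient a death date instead. A data manager who follows it would code an event, and the endpoint becomes time to death or loss to follow-up.

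The assigned death can never be later than the true one, so survival is understated. If one arm loses more patients than the other, the excess loss appears as excess mortality. If both arms lose patients, a real effect is diluted. With visits six months apart after month 6, the assigned death may also fall well before contact was actually lost.

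The word *usually* leaves it open which patients the rule applies to, in a trial whose participants are not blinded. The exclusion and imputation statements in the Data analysis section then point the same patients towards two other treatments.

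**Working it through.** **The rules side by side.** Take a patient who stops attending at month 8 with vital status unknown.

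| Source | Treatment of this patient |
|---|---|
| Overall survival, second sentence | Death dated at the last visit |
| Data analysis, incomplete follow-up | Left out of the efficacy analysis |
| Data analysis, missing data | Multiply imputed |

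These cannot all apply, and the text gives no order of precedence. No section says that the patient is censored.

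**The plan's own figure.** The document gives no number for OS. Its only sample-size figure is for a difference in months: 2 × [(1.96 + 0.842) × 1.8 / 1]² = 50.9, rounded to 51 per arm. It reproduces, and it does not depend on the OS rule. It is used below only as the number of patients.

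**Inputs for an illustration.** From the protocol: 51 per arm and 24 months of follow-up. Assumed, because the document does not give them: exponential survival, a true median of 8 months (range 6 to 18), loss fractions of 5% to 20%, and loss unrelated to prognosis.

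**Formulas.** Death hazard λ = ln 2 / median. Loss hazard c solves c/(λ + c) × [1 − exp(−24(λ + c))] = fraction lost. If loss counts as death, the event hazard is λ + c.

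At a median of 8 months, λ = 0.6931/8 = 0.08664. The solutions are c = 0.00516 (5% lost), 0.01078 (10%), 0.01695 (15%) and 0.02376 (20%).

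**Reported median = ln 2 / (λ + c).**
- 10% lost: 0.6931/0.0974 = 7.1 months.
- 20% lost: 0.6931/0.1104 = 6.3 months.
- With a true median of 12 months the reported values are 10.5 and 9.1, and 24-month survival falls from 25.0% to 20.5% and 16.2%.

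**Unequal loss, no true effect.** With 5% v 15% lost, about 3 v 8 of 51 patients, the apparent hazard ratio is (0.08664 + 0.01695)/(0.08664 + 0.00516) = 0.10359/0.09180 = 1.13. For medians of 6 to 18 months it is 1.12 to 1.18. The coded events number 51 × [(1 − exp(−24 × 0.09180)) + (1 − exp(−24 × 0.10359))] = 92. The expected log-rank statistic is √(92/4) × ln 1.128 = 0.58, so the two-sided 5% test rejects with probability Φ(0.58 − 1.96) + Φ(−0.58 − 1.96) = 0.09. Over medians of 6 to 18 months this is 9% to 10%.

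**Dilution of a true hazard ratio of 0.70** (control median 8 months, experimental death hazard 0.7 × 0.08664 = 0.06065):
- *Equal fraction lost in each arm.* The experimental loss hazards are 0.00854 (10%) and 0.01864 (20%). Apparent ratios: (0.06065 + 0.00854)/0.0974 = 0.71 and (0.06065 + 0.01864)/0.1104 = 0.72.
- *Equal loss hazard in each arm*, set by 10% or 20% loss in the control arm. Apparent ratios: (0.06065 + 0.01078)/0.0974 = 0.73 and (0.06065 + 0.02376)/0.1104 = 0.76. The experimental arm then loses about 12% or 24%, because its patients live longer and stay exposed to loss.

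**After the correction.** With censoring at the date last known alive and non-informative loss, the event hazard returns to λ. The median is then not distorted by the rule, and the hazard ratio is 1.00 when there is no effect, whatever the loss in each arm.

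**The case against.** The best defence is that the authors meant censoring. The first sentence of the OS definition, running to death or last follow-up, is the usual time variable for a censored analysis, and Kaplan-Meier is the named method. The second sentence fixes a time without separately stating an event code, and it is hedged. It may be loose wording and not a settled choice. That is a fair reason to speak of the rule as written. It does not rescue the sentence, which calls the date a time of death and is corrected nowhere else.

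A second objection is that the Data analysis section may take these patients out of the OS curve. If the exclusion covers OS, the bias shown above does not arise, but a different one does, from dropping randomised patients after the fact. A reader might therefore infer that the reported OS is bound to be biased by loss coded as death. The documents do not support that without condition; it depends on which of the three rules prevails.

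A reader might also quote 0.73 to 0.76 as the dilution under balanced loss. That needs equal loss hazards. With equal fractions lost, the effect is smaller.

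Finally, OS is secondary, and at 51 per arm the 5% v 15% example raises the false-positive rate only from 5% to about 9%. Both points stand and limit the weight of the finding.

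**Conclusion.** The concern holds for the text as it stands. The stated rule makes loss to follow-up a death, so a result obtained under it would not be overall survival. It also conflicts with the exclusion and imputation statements in the Data analysis section.

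The direction of the error under the rule is certain; its size is not. Under the assumptions above, moderate loss takes roughly one to two months off a true median of 8, a ten-point imbalance in loss produces a spurious hazard ratio of about 1.13, and a real effect is diluted slightly to moderately. None of these figures predicts this trial, because the document reports neither an OS median nor a loss rate.

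A reader might infer that the trial's main result is compromised. It is not by this sentence: iPFS has its own definition, and the sample size does not use OS.

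**What to change.** In the Overall survival section, define OS as time to death from any cause. Replace the sentence on lost patients with: *Patients not known to have died are censored at the date last known alive.* The word *usually* goes with it.

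In the Data analysis section, state that the exclusion for incomplete follow-up and the multiple-imputation rule do not apply to OS, so that all randomised patients enter the OS analysis. Counting loss as death may remain only as a labelled sensitivity analysis.

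The cost is a rewritten definition and one reconciling statement, settled before the OS analysis. It needs no new kind of data, since the last visit date is already used, and no change in sample size.
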